#### Sardinia study (randomising single GPs)

We expect to recruit about 900 General Practitioners. Such a sample would exceed the number needed to assess the same objectives described for the other study.

### Statistical analysis

The statistical analysis will be performed according to the intention-to-treat principle, analysing physicians' prescriptions according to the treatment group to which they were randomly allocated (as single GPs or as members of PCGs), and independently from their participation to the outreach visits. A 'modified intention to treat' will be considered in case some physician should not be actually offered the randomised intervention (for example, if pharmacists should become unavailable in a given area for organisational reasons or if health policy issues should arise, e.g. lack of agreement with medical syndicates, etc). Secondly, a by treatment analysis will also be performed considering only physicians who actually participated to the visits.

T-test (for continuing variables), chi-square test (for discrete variables) and multiple linear regression will be used, the latter to investigate how specific variables (like baseline prescriptions, region, size of PCG, size of assisted population, age and sex of GP, month of follow-up, etc) can affect outcomes. Analysis of covariance (ANCOVA) will be used for evaluating primary outcomes in case relevant baseline imbalances (for example in the prescription of targeted drugs) will make statistical adjustment necessary.

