**Methods/Design:**

Two RCTs are planned:

1) a two-arm cluster RCT, carried out in Emilia-Romagna and Friuli Venezia Giulia, will evaluate the effectiveness of small group meetings, randomising about 150 Primary Care Groups (corresponding to about 2000 GPs) to pharmacist outreach visits on two different topics. Physicians' prescriptions (expressed as DDD per 1000 inhabitants/day), knowledge and attitudes (evaluated through the answers to a specific questionnaire) will be compared for target drugs in the two groups (receiving/not receiving each topic).

2) A three-arm RCT, carried out in Sardinia, will evaluate both the effectiveness of one-to-one meetings (one pharmacist visiting one physician per time) and of a 'new' information format (compared to information already available) on changing physicians' prescription of specific drugs. About 900 single GPs will be randomised into three groups: physicians receiving a visit supported by "traditional" information material, those receiving a visit with "new" information material on the same topic and those not receiving any visit/material.

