#### Sardinia study (randomising single GPs)

A three-arm RCT is planned: single GPs will be randomised so that they may receive: an outreach visit from a trained pharmacist, supported by information material in a 'traditional' format as background material; the same kind of visit supported by an 'enriched' format (the type of bulletin used in the cluster study) [17]; or no visit at all (Fig. 2). Both the effectiveness of the outreach visit and of the information format will be evaluated (see outcomes).

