### Information retrieval

Monthly prescription data will be retrieved from provincial drug prescription databases. Although impossible to eliminate completely, information bias due to database accuracy should not affect our evaluation significantly, since limited error rates are expected.

In the cluster RCT, knowledge and attitudes of physicians will be evaluated through separate questionnaires distributed during the information meetings. Each set of questions will be topic dependent, therefore questionnaires will be developed for each topic. The additional file shows the questionnaires related to the first two topics.

The knowledge questionnaire will be 'nominal' and filling up it will be necessary for receiving CME credits, while the attitude questionnaire will be anonymous so that responders can express their views freely.

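### In Sardinia's visit versus no-visit contrast, the by-treatment analysis, and the modified intention-to-treat analysis if it drops only unserved visit-arm GPs, would set a selected group against unselected controls

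*Protocol article*

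**What the plan says.** All the analysis sets are in the Statistical analysis section of the protocol article, and they serve both trials.

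- **Lead set.** Intention to treat, "analysing physicians' prescriptions according to the treatment group to which they were randomly allocated", and "independently from their participation to the outreach visits".
- **Modified set.** "A 'modified intention to treat' will be considered in case some physician should not be actually offered the randomised intervention". The examples given are organisational or political, such as "if pharmacists should become unavailable in a given area for organisational reasons" or a failure to agree with the doctors' unions. The section does not say which GPs leave the analysis, from which arms, or whether this set replaces intention to treat or stands beside it.
- **By-treatment set.** "Secondly, a by treatment analysis will also be performed considering only physicians who actually participated to the visits".

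The Sardinia section describes two arms visited with different material and a third receiving "or no visit at all". In the cluster trial, by contrast, groups not allocated a topic receive a meeting on the other topic.

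Outcomes do not depend on a visit taking place. Under Information retrieval, "Monthly prescription data will be retrieved from provincial drug prescription databases", and Organizational characteristics makes the Local Health Authorities responsible for supplying these data for the whole study period.

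**The concern.** Both additional sets are defined by what happens after randomisation: whether a visit was offered, or whether it was attended. In the Sardinia control arm neither event can occur, so neither condition can be applied there. If visit-arm GPs are removed on these grounds and all controls are kept, the two sides differ by selection as well as by the intervention. Areas where delivery fails, and GPs who decline a visit, may well prescribe differently from the rest. Removing them from one side can then produce a difference with no intervention effect.

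The order of the text adds to the problem. The modified set comes before the word that introduces the secondary analysis, so a later analyst could treat it as part of the first tier. The Main outcome section also words the comparison by receipt of the information, not by allocation. Finally, the first objective is whether a large-scale programme can be delivered at all, so failures of delivery belong in the effect estimate.

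**Working it through.** **1. Where can the conditions occur?**

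| Contrast | Non-offer or non-attendance possible in |
|---|---|
| Sardinia, any visit vs no visit | visit arms only |
| Sardinia, traditional vs enriched format | both arms |
| Cluster trial, topic A vs topic B | both arms |

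Only the first row is one-sided. Taken literally, the by-treatment rule keeps only GPs who took part in a visit, which leaves that contrast with no controls. If controls are kept, attenders are compared with an unselected arm.

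**2. Size of the shift (illustration).** The plan states no figure on this point, so there is none to reproduce. Let e be the share of visit-arm GPs excluded and d their excess prescribing over the arm average, both assumed. With no true effect, the mean of the remaining GPs falls by e × d / (1 − e).

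- e = 0.05, d = 0.20: 0.010 / 0.95 = 1.1%
- e = 0.10, d = 0.20: 0.020 / 0.90 = 2.2%
- e = 0.10, d = 0.30: 0.030 / 0.90 = 3.3%

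The last two are about a fifth and a third of the 10% target in the sample size section.

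**3. Effect on the false-positive rate (illustration).** The document says "About 900 single GPs will be randomised into three groups". Equal allocation is assumed, giving 600 visited and 300 not visited. A coefficient of variation is backed out of the finasteride plus dutasteride row of Table 2 (ICC 0.08, 154 groups, 15 GPs per group), assuming two-sided 5% and 80% or 90% power, because alpha and power are not stated.

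- Design effect: 1 + 14 × 0.08 = 2.12
- Effective GPs per arm: 154 × 15 / 2 / 2.12 = 544.8
- CV = 0.10 × √(544.8 / 2) / (1.960 + 0.842) = 0.59 at 80% power; with 1.282 in place of 0.842, 0.51 at 90%

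Now let q be the share dropped from the visit arms and D the difference between dropped and retained GPs, as a fraction of the mean. The bias is q × D and the standard error is CV × √(1 / (600(1 − q)) + 1 / 300).

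| q | D | Bias, % of mean | Type I error (CV 0.59 to 0.51) |
|---|---|---|---|
| 10% | 10% | 1 | about 0.06 |
| 20% | 25% | 5 | 0.21 to 0.27 |
| 30% | 40% | 12 | 0.77 to 0.88 |

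**4. Does the way of excluding matter?** A simulation of 4,000 trials had no true effect, eight areas with means from −30% to +30% of the overall mean, a residual SD of 0.55, and the two highest-prescribing areas unserved.

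| Analysis set | Bias | Type I error |
|---|---|---|
| Intention to treat by allocation | 0.000 | 0.057 |
| Unserved areas removed from all arms | 0.000 | 0.055 |
| Unserved GPs removed from visit arms only | −0.086 | 0.51 |

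The formula in step 2 agrees with the last row. The two highest area means are 0.214 and 0.300, so d = 0.257 and e = 2/8 = 0.25, giving 0.25 × 0.257 / 0.75 = 0.086. The scenario is deliberately severe. It shows the contrast between the rules and does not forecast what would happen in this trial.

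**The case against.** The case on the other side is substantial.

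- **Intention to treat comes first.** Every GP is analysed as allocated, whatever the attendance. This stands: the lead result is not affected.
- **The modified set is conditional and its rule is open.** A reader might infer that it necessarily removes GPs from the visit arms alone. The document does not say so. Its examples are area-wide or policy-level, single GPs are randomised in Sardinia, and taking an affected area out of all three arms would preserve the randomised comparison. This stands, so the point about the modified set is conditional.
- **The by-treatment analysis is secondary, and such analyses are conventional.** True, but being secondary does not supply a valid comparator. The stated rule still gives either no control arm or an unselected one.
- **Definitions of analysis sets belong in the analysis plan.** Largely fair for the missing exclusion rule. It does not cover the by-treatment rule, which the article states outright, or the placing of the modified set ahead of the secondary analysis with no rank.
- **ANCOVA could correct the imbalance.** The plan provides for adjustment where relevant baseline imbalances arise, naming prescription of the targeted drugs as an example. That could remove part of the bias, but the adjustment is conditional and cannot be relied on to remove selection on unmeasured features of areas or GPs.
- **The magnitudes are assumed.** This stands, and in the mildest case above the type I error barely moves.

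**Conclusion.** The concern holds in a limited form. In Sardinia's visit versus no-visit contrast, the by-treatment analysis as worded is not a randomised comparison. A modified intention-to-treat set would share the fault if it removed only unserved visit-arm GPs. Nothing in the text prevents that, or prevents such a set from being presented ahead of intention to treat.

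Two wider readings are not supported. The main result is not compromised, because it is analysed by allocation. Nor does the one-sided problem extend to the cluster trial or to traditional versus enriched material, where exclusions can fall on both sides; selective attendance could still distort those comparisons, but not through this route.

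The illustrative bias runs from about 1% to 12% of the mean, depending wholly on assumed exclusion rates and prescribing differences. The 2.2-3.3% case is an example and not an estimate. The wording should be changed, but the lead analysis does not need to be redesigned.

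**What to change.** 1. State that intention to treat by allocation, with every randomised GP or Primary Care Group kept in its arm, is the sole primary analysis in both trials. Word the main outcome by allocation instead of by receipt.
2. Make any modified intention-to-treat analysis a sensitivity analysis. Where delivery collapses, remove the whole affected area or randomisation stratum from all arms, with the decision taken blind to outcome.
3. In Sardinia, replace the by-treatment visit versus no-visit comparison with a complier-average (instrumental variable) estimate that uses allocation as the instrument. In its simplest form this is the intention-to-treat difference divided by the proportion of visit-arm GPs actually visited. State its assumptions: control GPs receive no visit, and allocation affects prescribing only through the visit.
4. In the cluster trial, compare attenders with attenders of the other topic and label the result exploratory.

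The cost is wording and a small amount of analysis. The prescription data are to be collected whether or not a visit takes place, and pharmacists already log their meetings. There are two downsides. The intention-to-treat effect may be diluted by non-delivery, although that is the pragmatic effect the trial sets out to measure. The complier estimate is less precise: if 20% of visit-arm GPs were not visited (assumed), the estimate and, approximately, its standard error would both be multiplied by 1 / 0.8 = 1.25.

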## Methods/Design

### Study population

#### Emilia-Romagna and Friuli Venezia Giulia study (cluster RCT)

Primary Care Groups (PCGs) will be the unit of randomisation (cluster). PCGs are defined as small groups, ranging from about 10 to 20 general practitioners (GPs) and assisting about 8,000 to 25,000 people in a defined area. A general rule is to include PCGs with less than or equal to 20 GPs. Exceptions may be accepted (considering the pragmatic nature of the study) but should be adequately justified by Local Health Authorities recruiting them. In any case, the proposal to split groups with more than 20 subjects will be made.

Local Health Authorities, which are in charge of the local organization of the study, should actively promote the information meetings by making them part of compulsory education and/or providing CME credits.

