### Sample size estimates

#### Emilia-Romagna and Friuli Venezia Giulia study (cluster RCT)

From a sample of 40 clusters (about 600 physicians) and using a dedicated software (Cluster Randomisation Sample Size Calculator version 1.0.2, Health Services Research Unit, Aberdeen University) we estimated the intracluster correlation coefficients (ICC) and the sample size that would be required to see a difference of 10% in the prescription of a number of possible drugs (15% for bisphosphonates), assuming an average cluster (PCG) size of 15 (Table 2).

**Table 2 T2:** Estimates of sample sizes to detect a prescribing difference of 10% (with two-tailed test)

	ATC code	Estimate of ICC	Sample size (NCP)
macrolides	J01FA	0.024	68
fluoroquinolones	J01MA	0.030	68
antidepressants	n06ab	0.058	88
nitroderivatives	C01da02, 05,08,14	0.09	96
bifosphosphonates **(15% diff)**	M05ba	0.062	106
proton pump inhibitors	A02BC	0.087	108
phosphomicine	J01xx01	0.014	108
Alfa blockers (for IPB)	g04ca + g04bx49	0.075	116
doxazosin (for IPB)	c02ca04	0.038	128
long acting β2 broncodilators + corticosteroids	R03AK06 e R03AK07	0.092	148
Finasteride +dutasteride	g04cb	0.08	154
opioids	N02A	0.061	164
clarithromicine	J01fa09	0.02	172
esomeprazole	A02bc05	0.023	204
long acting β2 broncodilators	R03AC12 e R03AC13	0.033	208
alendronate	M05ba04	0.08	218
finasteride	g04cb01	0.1	220
salmeterol + corticosteroids	R03ak06	0.102	234
bifosphosphonates	M05ba	0.062	238
azitromicine	J01fa10	0.068	266
risedronate	M05ba07	0	374
norfloxacine	J01ma06	0.055	386
fentanyl	N02ab03	0.043	428
salmeterol	R03ac12	0.053	698
morphine	N02aa01	0.05	2224
buprenorphine	N02ae01	0	Nc
bicalutamide	l02bb03	0	Nc
escitalopram	N06ab10	0	1434
levocetirizine	R06ae09	0.032	>600
antiandrogens	L02bb01+ L02bb03	0	nc

Since we expect to recruit about 150 PCGs we choose for the first round of information meetings the two topics previously described ('drugs for the treatment of benign prostatic hyperplasia', and 'drugs for the primary prevention of osteoporotic fractures in elderly people') because of the clinical relevance of the information to be presented.

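### The analysis section names only ordinary tests for a trial that randomises PCGs and makes no allowance for clustering; if they are run on GPs, an assumed 5% test would run at about 14–18% for ICCs of 0.062–0.08

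*Protocol article*

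**What the plan says.** For the Emilia-Romagna and Friuli Venezia Giulia trial, Study population states "Primary Care Groups (PCGs) will be the unit of randomisation (cluster". Sample size estimates follows that design: from 40 PCGs, "we estimated the intracluster correlation coefficients (ICC) and the sample size that would be required to see a difference of 10" per cent (15 for bisphosphonates), "assuming an average cluster (PCG) size of 15 (Table 2". About 150 PCGs are expected.

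The Statistical analysis section covers this trial and the Sardinia trial, where GPs are randomised singly, with one set of methods: "T-test (for continuing variables), chi-square test (for discrete variables) and multiple linear regression will be used". ANCOVA is added for primary outcomes if relevant baseline imbalance appears. Nothing in the section mentions clustering.

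The unit of analysis is not stated. The intention-to-treat sentence speaks of "analysing physicians' prescriptions according to the treatment group to which they were randomly allocated (as single GPs or as members of PCGs"). The regression covariates are given as "like baseline prescriptions, region, size of PCG, size of assisted population, age and sex of GP, month of follow-up, etc". The by-treatment analysis is restricted to individual physicians who attended.

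**The concern.** GPs in one PCG attend the same meeting with the same pharmacist, and the plan's own ICCs show that for most of the target drugs they also prescribe alike. A t-test or ordinary regression with one row per GP treats them as independent. Its standard error is then too small, its intervals too narrow and its p-values too low. The sample size allows for the correlation, but the named analysis does not say that it will.

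The main outcome of four planned comparisons is at stake. The economic evaluation goes ahead only if the meetings prove more effective than no meetings, so a false positive would carry into it.

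**Working it through.** **The plan's own figures.** The article states no error rate for the analysis. The PCG counts in Table 2 cannot be rebuilt, because alpha, power, mean and SD are not given. One internal check is possible. The required number should scale with the inverse square of the difference, and the two bisphosphonate rows agree: 238/106 = 2.245 against (15/10)² = 2.25.

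**Inputs**
- Cluster size m: 15 (Sample size estimates), or 2000 GPs / 150 PCGs = 13.3 (Abstract).
- ICCs (Table 2): 0.08 for "Finasteride +dutasteride" and for alendronate; 0 for risedronate; 0.062 for bisphosphonates as a class. Under Outcomes, the first three are main indicators. The fourth main indicator, the alpha-blocker ratio, has no ICC in the table.
- Level: two-sided 5%, assumed. Table 2 says only that the test is two-tailed.

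**Formula** for a GP-level test that ignores PCG: design effect DE = 1 + (m − 1) × ICC; actual type I error = 2 × [1 − Φ(1.96/√DE)].

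| ICC | m | DE | Type I error | Interval should be wider by √DE |
|---|---|---|---|---|
| 0 (risedronate) | any | 1 | 5.0% | 1.00 |
| 0.062 | 13.3 | 1 + 12.3 × 0.062 = 1.763 | 14.0% | 1.33 |
| 0.062 | 15 | 1 + 14 × 0.062 = 1.868 | 15.2% | 1.37 |
| 0.08 | 13.3 | 1 + 12.3 × 0.08 = 1.984 | 16.4% | 1.41 |
| 0.08 | 15 | 1 + 14 × 0.08 = 2.12 | 17.8% | 1.46 |

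**Simulation check** (75 PCGs per arm, 15 GPs each, 10,000 runs per ICC, no true effect). The GP-level t-test rejected in 5.2% of runs at ICC 0, 15.8% at 0.062 and 17.9% at 0.08. A t-test on PCG means rejected in 5.1%, 5.2% and 4.8%.

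**Effect of stratification.** Randomisation is stratified within Local Health Authority (LHA), so variation between LHAs largely cancels from the comparison. The documents do not say how much of the between-PCG variance this is. Assume a share s at total ICC 0.08 and m = 15. The effective DE is then 0.92 + 15 × 0.08 × (1 − s):
- s = 0.25: 0.92 + 0.90 = 1.82, type I error about 15%
- s = 0.50: 0.92 + 0.60 = 1.52, about 11%
- s = 0.75: 0.92 + 0.30 = 1.22, about 8%

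**The case against.** The strongest reply is that no sentence says the tests are run on GPs. DDD per thousand inhabitants per day is a population rate that can be computed per PCG, and a t-test or ANCOVA on PCG values would satisfy the quoted sentence and hold its level. The phrase about GPs as members of PCGs describes allocation under intention to treat. The GP-level covariates belong to a regression whose stated purpose is to explore influences on outcome. One paragraph serves two trials, and in Sardinia the simple tests face no PCG clustering.

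Much of this stands. The GP as unit is an inference, and the inflation is conditional on it. The objection does not remove the point, because the tests are valid in the cluster trial only under a condition that the section never states, and most of its wording leans the other way. Nor does it cover chi-square, which compares counts of individuals. Discrete questionnaire answers collected at PCG meetings would be clustered too.

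Three stronger readings are tempting, and the documents support none of them:
- **That the plan prescribes a GP-level analysis and so contradicts its sample size.** The section is silent on clustering, so the charge is an unstated allowance.
- **That the error rate is 15–18% throughout.** Risedronate's listed ICC is 0, the ratio has none, 0.062 is a class value and not that of a main indicator, and stratification or baseline adjustment may lower the figure.
- **That far larger inflation follows from monthly rows or from chi-square on individual patients.** Month is a regression covariate, but nothing says that monthly rows would be treated as independent in the main comparison. Nothing says that chi-square is applied to patients, and neither correlation is given.

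**Conclusion.** The point holds in conditional form. For a trial that randomises PCGs and is sized with ICCs, the plan names only methods for independent observations, makes no allowance for PCG clustering, and leaves a unit of analysis that reads as the GP.

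Followed that way, a nominal 5% test would run at about 14–18% over ICCs of 0.062–0.08. For finasteride plus dutasteride and for alendronate it would be about 16–18%, with intervals that ought to be about 1.4–1.5 times as wide. These figures assume a two-sided 5% level, equal cluster sizes of 13.3–15, the unadjusted ICCs of Table 2 and no gain from stratification. For risedronate there is no inflation at the listed ICC. For the alpha-blocker ratio the size is unknown.

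The omission itself is certain. The size depends on the unit actually used.

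**What to change.** State in the Statistical analysis section that every comparison in the cluster trial uses the PCG as the unit of inference, by one of two routes:
- a t-test or ANCOVA on one summary per PCG, such as DDD per 1000 inhabitants per day over the six-month follow-up; or
- a mixed model or GEE with PCG as the cluster, plus a GP-level random effect if monthly rows are used.

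For discrete outcomes in the cluster trial, replace chi-square with a cluster-adjusted method, such as PCG-level percentages, or GEE or mixed logistic regression. Questionnaires then need a PCG code, which need not identify the physician. Keep the simple tests for Sardinia, with one value per GP.

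The cost is wording. No further prescribing data are needed. The downside is wider intervals, which reflect the precision that the design actually has.

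### The cluster trial randomises PCGs and is sized with ICCs, but its listed tests make no allowance for PCG; if run on individual GPs, they give about 16–18% false positives where the ICC is 0.08

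*Protocol article*

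**What the plan says.** For the cluster trial, the Study population section states: "Primary Care Groups (PCGs) will be the unit of randomisation (cluster". Under Sample size estimates, the authors report that from 40 clusters "we estimated the intracluster correlation coefficients (ICC" and derived the number of PCGs needed, "assuming an average cluster (PCG) size of 15 (Table 2".

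The Statistical analysis section covers the cluster trial and the Sardinia trial together. Its intention-to-treat sentence describes "analysing physicians' prescriptions according to the treatment group to which they were randomly allocated (as single GPs or as members of PCGs". The methods follow: "T-test (for continuing variables), chi-square test (for discrete variables) and multiple linear regression will be used". For adjustment, "Analysis of covariance (ANCOVA) will be used for evaluating primary outcomes in case relevant baseline imbalances" make it necessary.

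The section names no PCG-level summary, PCG random effect or cluster-robust variance. The size of the PCG is listed as a regression covariate, but the PCG itself is not.

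**The concern.** GPs in one PCG are allocated together and attend the same meeting, and Table 2 reports that their prescribing is correlated for most drugs. A t-test, chi-square test, regression or ANCOVA that treats those GPs as independent understates the standard error of the difference between arms. The sample size allows for the correlation; the listed tests, read as they stand, do not. This would hold even with a single six-month value per GP, so it is a separate matter from how monthly data are handled.

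An ineffective meeting could be declared effective well above the nominal rate. The consequences reach further than the p-value. Under Economic analysis, the economic evaluation is carried out only if meetings prove more effective than none, and its sensitivity analysis uses the confidence limits of the effect. Limits that are too narrow would carry through.

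**Working it through.** **Inputs from the Protocol article**

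- About 150 PCGs and 2000 GPs (Abstract: "randomising about 150 Primary Care Groups (corresponding to about 2000 GPs"), so 2000/150 = 13.3 GPs per PCG. The planning value is 15, and the stated range of PCG sizes is about 10 to 20.
- ICCs from Table 2: finasteride plus dutasteride 0.08, alendronate 0.08, bisphosphonates 0.062, risedronate 0.
- Main indicators (Outcomes section): 5 alpha-reductase inhibitors and the alpha-blocker ratio for prostatic hyperplasia; alendronate and risedronate for osteoporosis. Table 2 has no ICC for the ratio, and the autumn topics were not yet chosen.
- Nominal alpha: not stated. Table 2 says only that the test is two-tailed. I assume 5%.

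**The plan's own figures.** The article gives no SD, power or alpha, so the absolute PCG numbers in Table 2 cannot be reproduced. One internal check is possible, because the required number scales with 1/difference². For bisphosphonates, going from a 10% to a 15% difference gives 238/(0.15/0.10)² = 238/2.25 = 105.8, which rounds up to the printed 106.

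**False-positive rate of a GP-level test that ignores PCG**

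Design effect DE = 1 + (m − 1) × ICC. The true standard error is √DE times the one reported. Actual two-sided error = 2 × [1 − Φ(1.96/√DE)].

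| Indicator | ICC | m | DE | √DE | Actual error |
|---|---|---|---|---|---|
| Finasteride + dutasteride; alendronate | 0.08 | 13.3 | 1 + 12.33 × 0.08 = 1.987 | 1.41 | 16.4% |
| Same | 0.08 | 15 | 1 + 14 × 0.08 = 2.12 | 1.46 | 17.8% |
| Bisphosphonates (class) | 0.062 | 13.3 | 1 + 12.33 × 0.062 = 1.765 | 1.33 | 14.0% |
| Same | 0.062 | 15 | 1 + 14 × 0.062 = 1.868 | 1.37 | 15.2% |
| Risedronate | 0 | any | 1 | 1 | 5.0% |

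Over the stated PCG sizes at ICC 0.08, the error runs from 13.5% (m = 10, DE 1.72) to 21.7% (m = 20, DE 2.52).

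**Simulation check** (150 equal-sized PCGs, no true effect, 8000 runs per scenario)

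| ICC | m | t-test on GPs | t-test on PCG means |
|---|---|---|---|
| 0.08 | 13 | 16.5% | 5.4% |
| 0.08 | 15 | 18.3% | 4.9% |
| 0.062 | 15 | 14.9% | 4.8% |
| 0 | 15 | 4.7% | 4.9% |

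**Stratification.** Allocation is stratified within Local Health Authority (LHA) and by PCG population. If half of an ICC of 0.08 were variation between LHAs that the allocation balances (an assumption; the article gives no split), a rough value comes from using ICC 0.04. At m = 13.3, DE = 1 + 12.33 × 0.04 = 1.493 and the error is about 11%.

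**The case against.** A reader might infer that the plan commits the cluster trial to a GP-level t-test as its main test, with 16–18% error on every topic. The document does not support that.

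- **Level of the test.** The Statistical analysis section does not say at what level the t-test is run. The main outcome, DDD per thousand inhabitants per day, is a population rate that can be computed per PCG, and a t-test on PCG values is valid. The phrase about physicians' prescriptions sits in a sentence that defines intention-to-treat membership.
- **Covariates.** GP age and sex belong to the regression, and the paragraph also serves Sardinia, where GPs are randomised. They suggest GP-level data but do not prove it.
- **Main test.** None is ranked as primary.
- **Reach of the figure.** Risedronate is also a main indicator and has a printed ICC of 0. The alpha-blocker ratio and the autumn topics have no tabulated ICC. The 5% level is assumed.
- **Knowledge.** This is scored as a number of correct answers, which the chi-square test does not clearly cover.
- **Condensed article.** A fuller document may specify a cluster analysis, and authors who estimated ICCs may well have intended one.

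All of this limits the claim, and the verdict is worded accordingly. It does not remove the problem. Silence alone would be no finding, but the section is not silent: it names methods, words them around physicians, gives the same list for a cluster trial and an individually randomised one, and defines the by-treatment analysis by selecting individual physicians. Followed as written, it leads most naturally to an analysis that disregards the clustering used in the sample size.

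**Conclusion.** The concern holds in conditional form. The analysis text is inconsistent with the cluster design and with Table 2, and it permits an invalid test of the primary outcome. If the listed tests are applied to individual GPs, at an assumed nominal two-sided 5%:

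- about 16–18% false positives for finasteride plus dutasteride and for alendronate (ICC 0.08, 13.3 to 15 GPs per PCG), roughly three times the nominal rate;
- about 14–15% for bisphosphonates as a class;
- no inflation for risedronate;
- unknown for the alpha-blocker ratio and the autumn topics.

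The rates would be lower, about 11% in the illustration above, if stratified allocation removes part of the ICC. The Sardinia trial is not affected. Because validity of the primary inference is at stake for two of the first-round main indicators, the text should be corrected before analysis.

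**What to change.** In the Statistical analysis section, state that prescribing outcomes of the cluster trial, including the ANCOVA and regression analyses, are analysed in one of two ways:

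- one value per PCG, compared between about 75 and 75 PCGs; or
- a GP-level model with a PCG random effect or cluster-robust standard errors.

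Apply the same principle to questionnaire outcomes where forms can be linked to a PCG meeting, with a model suited to the outcome type. The attitude form is anonymous, so whether it can be linked needs checking. Reserve plain GP-level tests for Sardinia. Use the cluster-correct confidence limits in the economic sensitivity analysis.

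The cost is a sentence and slightly more programming, with no extra recruitment. For indicators with ICC 0.08, intervals become about 1.4 times as wide as the naive ones (1.41 to 1.46 from the working), which is the loss of precision that Table 2 already built in.
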